**34.9 Kg/m2**

**Eligibility: Inclusion/Exclusion criteria are satisfied**

**5 Cases**

**5 Controls**

**5 Cases**

**5 Controls**

**5 Cases**

**5 Controls**

**5 Cases**

**5 Controls**

**Enrollment**

**4. Patient Eligibility and Exclusion Criteria**

*a. General Inclusion criteria valid for both trials*

1. Age 50-75 years
2. BMI 23-34.9 kg/m2
3. Estimated GFR >60 mL/min
4. Blessed mental score equal to or less than 3
5. Ability to fully participate in an informed consent process

6. For Trial A (UA versus Placebo): all participants should have UA ≤10.0 mg/dL

7. For Trial B (Rasburicase versus Placebo): all participants should have UA ≤10.0 mg/dL

*b. General Exclusion criteria for potential participants of both trials*

1. Uric Acid level greater than 10.0 mg/dL.
2. History of hypersensibility or intolerance to Rasburicase and/or to Lithium
3. Chronic Kidney Disease.
4. History of kidney stones.
5. History of asthma, atopic allergies, hemolytic or methemoglobinemia reactions
6. History of unstable angina, cardiac arrhythmia, stroke or myocardial infarction within 3 months, open-heart surgery within 6 months of the study enrollment
7. History of drug or alcohol dependence, or positive urine toxicology
8. Past or present positive test for HBV, HCV or HIV (base on blood test).
9. Glucose-6-Phosphate Dehydrogenase deficiency (G6PD-deficiency)*
10. History of gout
11. Last menstruation occurred less than 1 year ago
12. Unintentional or intentional weight loss of 5 kg in the previous 6 months
13. Alcohol daily intake >30 grams (more than 2 beers daily, more than 2 glass of wine or cocktail daily)
14. Current smokers or former smokers (stopped smoking less than 1 year before)
15. Blood pressure > 150/90 mmHg
16. Diabetes mellitus on dietary or pharmacological treatment
17. Hb <11.5 g/dL in women or < 12.5 g/dL in men
18. Acute infection/inflammation (CRP>5 mcg/mL) for Trial A: UA versus Placebo, CRP >10mcg/L for Trial B: Rasburicase versus Placebo, or any clinical overt chronic infections including periodontal disease.
19. Active liver disease or liver function tests greater than 2 times upper normal limit
20. Self reported inflammatory joints or autoimmune diseases
21. Treatment over the last 3 months with Allopurinol, Rasburicase
22. Treatment over the last 3 months with Warfarin, Dicumarol, Theophylline, Statins
23. Necessity of daily treatment with NSAID
24. Current hormone replacement

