25. Ongoing glucocorticoids, corticosteroids, including prednisone and/or cortisone injections or inhalations. (topical steroid cream use and occasional corticosteroid administration over the last 3 months is acceptable)
26. Current daily antioxidants or/and multivitamin supplementation or over the last month
27. Life-threatening diseases including malignancies
28. Recent Blood Donation (last 56 days)
29. Any other reason that based on the PI’s judgment requires exclusion from this study
30. Inability to obtain venous access.

*The Glucose-6-Phosphate Dehydrogenase activity will be assessed in each eligible participant randomly assigned to Trial B. The test for G6PD deficiency will require 3.5 ml of blood.

#Participants will be asked to refrain from taking any NSAIDs during the five days prior before the baseline evaluation and over the course of the study with the exception of Aspirin 100 mg/daily or less.

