Among the 703 patients the most serious adverse reactions were allergic reactions including anaphylaxis (<1%), rash (1%), hemolysis (<1%), and methemoglobinemia (<1%). Signs and symptoms of these reactions include bronchospasm, chest pain and tightness, dyspnea, hypoxia, hypotension, shock, and/or urticaria. Rasburicase administration should be immediately and permanently discontinued in any patient identified as having developed hypersensitivity reactions, hemolysis[[1]](#footnote-2) or methemoglobinemia[[2]](#footnote-3). Additional adverse reactions were fever (5%), neutropenia with fever (4%), respiratory distress (3%), sepsis (3%), neutropenia (2%), and mucositis (2%). The following adverse reactions were observed in <1% of patients regardless of causality: acute renal failure, arrhythmia, cardiac failure, cardiac arrest, cellulitis, cerebrovascular disorder, chest pain, convulsions, cyanosis, diarrhea, dehydration, hot flashes, ileus, infection, intestinal obstruction, hemorrhage, myocardial infarction, paresthesia, pancytopenia, pneumonia, pulmonary edema, pulmonary hypertension, retinal hemorrhage, rigors, thrombosis, and thrombophlebitis.

Immunogenicity: Rasburicase is immunogenic in healthy volunteers, and can elicit antibodies that inhibit the activity of rasburicase *in vitro.* In a study of 28 healthy volunteers, the incidence of antibody responses to either a single dose or to 5 daily doses was assessed. Binding antibodies to rasburicase were detected by ELISA in 17/28 (61%) volunteers and neutralizing antibodies were detected in 18/28 (64%) volunteers. Time to detection of antibodies ranged from 1 to 6 weeks after ELITEK exposure. In two subjects with extended follow-up, antibodies persisted for 333 and 494 days.

Storage: Rasburicase will be securely stored in the NIA Research Pharmacy under the appropriate conditions.

Mechanism of Drug Accountability: All dispensing of Rasburicase will be documented on a Protocol Specific Investigational Agent Accountability Record maintained in the NIA Research Pharmacy.

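### The 3-month look-back for prior rasburicase in exclusion item 21 does not fit the protocol's own antibody data; a minor point, mainly about safety, that a one-line reconciliation would settle

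*Protocol*

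**What the plan says.** Protocol section 4, list b, applies to both trials. Item 21 excludes "Treatment over the last 3 months with Allopurinol, Rasburicase". Rasburicase and allopurinol share the same look-back, and no other item mentions past rasburicase unless it caused a problem. Item 2 excludes "History of hypersensibility or intolerance to Rasburicase and/or to Lithium".

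Section 14, under Rasburicase, Immunogenicity, says that the drug "can elicit antibodies that inhibit the activity of rasburicase" in vitro. In 28 healthy volunteers, "the incidence of antibody responses to either a single dose or to 5 daily doses was assessed". The results were: "Binding antibodies to rasburicase were detected by ELISA in 17/28 (61%) volunteers and neutralizing antibodies were detected in 18/28 (64%) volunteers". Antibodies appeared between 1 and 6 weeks after exposure. On duration: "In two subjects with extended follow-up, antibodies persisted for 333 and 494 days".

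Two other places bear on this. Under Toxicities, section 14 says that safety and efficacy are well established for one course of treatment and that the study uses the drug in that way. Section 6 notes that antibodies have been seen after a single dose, then declares the issue not applicable because rasburicase is not approved in adults.

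**The concern.** A 3-month look-back answers one question: is an earlier dose still affecting uric acid? It does not answer another that the protocol itself raises: might the person still carry antibodies from that dose? On the only persistence figures given, they might, well beyond 3 months.

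The stake is mainly safety. The Trial B volunteers are healthy and, by section 17, are not expected to gain direct medical benefit. Section 6 names anaphylaxis and other hypersensitivity among the drug's most severe effects. For a person admitted more than 3 months after an earlier exposure, the study infusion would be a second course, whereas section 14 rests its safety statement on a single one. A secondary stake is interpretation, since section 11 assumes that rasburicase takes uric acid to zero.

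**Working it through.** **Inputs**

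- Look-back: 3 months, taken as 90 to 92 days (section 4, item 21).
- Antibody incidence: 17/28 binding and 18/28 neutralising (section 14, Immunogenicity).
- Time to detection: 1 to 6 weeks. Persistence: 333 and 494 days, two subjects (same place).
- Elimination half-life: 18 hours (section 14, Clinical pharmacology).
- Treated participants in Trial B: 10 (sections 3 and 5).

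**1. The protocol's own percentages.** 17/28 = 60.7% and 18/28 = 64.3%, matching the stated 61% and 64%. Exact (Clopper-Pearson) 95% intervals are 40.6% to 78.5% and 44.1% to 81.4%. The text does not separate the single-dose recipients from the five-dose recipients.

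**2. Window against persistence.**

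| Reported persistence | In months (÷ 30.44) | Multiple of 92 to 90 days | Days beyond the window |
|---|---|---|---|
| 333 days | 10.9 | 3.6 to 3.7 | 241 to 243 |
| 494 days | 16.2 | 5.4 to 5.5 | 402 to 404 |

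The latest reported detection time, 6 weeks, is 42 days. A person at day 90 is therefore past the reported period of onset and, on these two cases, still within the reported period of persistence.

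**3. Window against washout.** 90 days × 24 h ÷ 18 h = 120 half-lives. For clearing the drug the window is ample. It falls short only as an immunogenicity criterion.

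**4. Does another criterion close the gap?**

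- Item 2 needs a known reaction or intolerance, so it misses exposure without symptoms.
- Item 5 removes people with asthma, atopy or past hemolytic or methemoglobinemia reactions. It does not ask about exposure.
- Item 27, "Life-threatening diseases including malignancies", removes most people likely to have had the drug, but does not clearly reach cancer treated in the past.
- Item 29, "Any other reason that based on the PI’s judgment requires exclusion from this study", permits exclusion but states no rule on past rasburicase.
- No test for antibodies to rasburicase is listed among the screening tests or in the schedule of visits.

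**5. Does section 6 settle it?** Its reason is that the drug is not approved in adults. Section 14, under Dose, speaks of an FDA-approved dose in pediatric and adult patients. The clinical pharmacology text in the same section describes adult use, including 387 adults in one compassionate-use trial. The antibody data come from healthy volunteers. The reason given conflicts with the rest of the document.

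**6. Illustrative dilution.** Assume that *k* of the 10 treated participants have complete neutralisation in vivo, which the protocol does not report. The mean fall in uric acid is then multiplied by 1 − *k*/10: 1.0 for none, 0.9 for one, 0.8 for two. Applied to the median fall of 4.1 mg/dL that section 14 gives for patients below 8 mg/dL, one such participant leaves 4.1 × 0.9 = 3.7 mg/dL. Section 11 claims power of 0.92 to 0.93 for a change of 2.0 mg/dL.

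**The case against.** The strongest reply is that almost nobody is affected. Section 14 describes rasburicase as a drug for cancer patients, while the trial enrols community-dwelling people aged 50 to 75 and excludes malignancies. The criteria on kidney function, weight loss, hemoglobin, CRP, liver tests and steroids narrow the group further. A physician also reviews each medical history, so item 21 admits nobody by itself. And item 21 reads naturally as a urate-lowering washout, for which 3 months is ample. All of this stands. It sets the size of the point without removing it: the criteria narrow the gap but none covers a past exposure that caused no symptoms.

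The evidence is also thin, and this stands too. Persistence comes from two subjects, and the text does not say that their lasting antibodies were neutralising. Inhibition is described in vitro. Nothing in the protocol links antibody status to a reaction on re-exposure or to a failed fall in uric acid.

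A reader might infer that Trial B is set to re-expose sensitised people in whom the drug fails, so that its exposure contrast is compromised. The document does not support this. The 10% loss per participant assumes complete neutralisation in vivo, and even then the remaining contrast stays above the 2.0 mg/dL for which section 11 still claims power above 0.9, taking those claims as stated.

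The single-course sentence can be read as describing only what happens within the study. On that reading it does not formally contradict item 21, but the safety basis it states still does not extend to a second course.

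**Conclusion.** The mismatch is real but minor, and mainly a safety matter. The look-back in item 21 is roughly a quarter to a fifth of the antibody persistence that section 14 reports, and the reason in section 6 for setting immunogenicity aside conflicts with section 14. The protocol names prior rasburicase as an entry concern, so the criterion should agree with the protocol's own account of the drug.

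The conclusion rests on taking the two persistence times as possible durations, not typical ones, and on the absence of any listed criterion for exposure without symptoms. The protocol gives no figure for how many candidates have had rasburicase; the expected number is very small and may well be zero. Any effect on the uric acid contrast or on power is speculative.

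A reader might also conclude that a particular longer window or a lifetime exclusion is required. The document does not establish either. It shows only that the present window and the immunogenicity data do not fit together.

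**What to change.** Separate rasburicase from allopurinol in item 21, so that prior rasburicase has its own criterion. Reconcile that criterion with section 6 (the note on immunogenicity) and section 14 (adult use and approval, the single-course statement, and the antibody incidence and persistence). If the sponsor judges the present window adequate despite those data, the protocol should say why, on grounds that do not conflict with section 14. The form of the revised criterion is for the sponsor to decide.

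The cost is one line in the exclusion list, with matching wording in section 6, and almost no lost candidates. Sample size, schedule and analysis are unaffected.

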**5. Procedures and Therapeutic Plan**

In each of the two Trials, 5 women and 5 men will be assigned to receive treatment and 5 women and 5 men will be assigned to receive placebo. There will be no recognizable labels treatment/placebo on the drug bag, and the NIA research pharmacist will be the only person unblinded to the random assignment to treatment or placebo.

**Trial A: UA versus placebo**

Treatment: UA 500 mg in 250 ml of 0.1% lithium carbonate/ 4% dextrose solution infused over a 60 minute period on visit 3.

Placebo: 250 ml of 0.1% lithium carbonate/ 4% dextrose solution infused over a 60 minute period on visit 3.

**Trial B: Rasburicase versus Placebo**

Treatment: Rasburicase 0.15 mg/kg in 250 ml 0.9% sodium chloride solution infused over a 60 minute period on visit 3.

Placebo: 250 ml of 0.9% sodium chloride solution infused over a 60 minute period on visit 3.

Both treatment and placebo administration will be done only once and according to the same procedures. Treatment and placebo administration will be done in double-blind fashion and under continuous physician’s supervision. Only the NIA research Pharmacist or someone designated by him will be aware of the participant random assignment to treatment or placebo.

**Schedule of visits**

For each Trial, participants will be scheduled for a total of 4 visits including one overnight stay lasting 2 nights and will undergo the same clinical and laboratory procedures. The table below summarizes the tests and procedures to be done during each of the visit. After 2 weeks, participants will be considered off study.

**Clinical and laboratory procedures in both trials**

The clinical and laboratory procedures will be articulated into two main steps. The first part will be a screening of the potential participants, while the second part will be a comprehensive assessment of participants’ clinical characteristics and collection of blood samples. Blood drawn during the screening visit will be sent to Harbor Hospital. On subsequent visits, sample for assay of the inflammatory markers will be sent to the core lab, divided into aliquots banked at the NIA’s Core Lab, and at the end of the study sent to the different laboratories to perform the appropriate assays.

|  | **Visit 1**  **(T0)** | **Visit 2**  **(T1)** | | | | | | **Visit 3**  **Inpatient**  **(T2)** | | | | | | | | | | | | | **Visit 4**  **(T3)** |
| --- | --- | --- | --- | --- | --- | --- | --- | --- | --- | --- | --- | --- | --- | --- | --- | --- | --- | --- | --- | --- | --- |
|  | Outpatient | Outpatient  (up to 1 week after Visit 1 and 2 days before Visit 3) | | | | | | Day 1 | | | | | | | Day 2  (24 h from intervention is the baseline for the second Oral Lipid Tolerance Test) | | | | | | Outpatient |
| **Type of Visit** | Screening | Baseline | 0h | 2h | 4h | 6h | 8h | Baseline | Intervention | 1 h | 2 h | 4 h | 8 h | 12 h | 24 h | 0 h | 2 h | 4 h | 6 h | 8 h | 2 weeks |
| Medical History/  Physical Exam | X | X |  |  |  |  |  |  |  |  |  |  |  |  |  |  |  |  |  |  | X |
| EKG | X |  |  |  |  |  |  |  |  |  |  |  |  |  | X |  |  |  |  |  | X |
| HIV, HBV, HCV | X |  |  |  |  |  |  |  |  |  |  |  |  |  |  |  |  |  |  |  |  |
|  |  |  |  |  |  |  |  |  |  |  |  |  |  |  |  |  |  |  |  |  |  |
| Blood tests1 | X |  |  |  |  |  |  |  |  |  |  |  |  |  | X |  |  |  |  |  | X |
| Urine analysis | X |  |  |  |  |  |  |  |  |  |  |  |  |  |  |  |  |  |  |  | X |
| Urine Toxicology2 | X |  |  |  |  |  |  |  |  |  |  |  |  |  |  |  |  |  |  |  |  |
| Urine Pregnancy | X | X |  |  |  |  |  | X |  |  |  |  |  |  |  |  |  |  |  |  |  |
| Urine Specific Gravity |  |  |  |  |  |  |  | X |  |  | X |  |  |  | X |  |  |  |  |  |  |
| Urine PH |  |  |  |  |  |  |  | X |  |  | X |  |  |  | X |  |  |  |  |  |  |
| Urine for Uric Acid |  |  |  |  |  |  |  | X |  | X | | | | | X |  |  |  |  |  | X |
| Eligibility, Consent | X |  |  |  |  |  |  |  |  |  |  |  |  |  |  |  |  |  |  |  |  |
| Randomization |  |  |  |  |  |  |  | X |  |  |  |  |  |  |  |  |  |  |  |  |  |
| Lipid Tolerance Test3 |  | X |  | X | X | X | X |  |  |  |  |  |  |  | X |  | X | X | X | X |  |
| Basal Metabolic Rate |  |  |  |  |  |  |  | X |  |  |  |  |  |  | X |  |  |  |  |  |  |
| Vital signs | X | X |  |  |  |  | X | X |  | X | X | X | X | X | X |  |  |  |  | X | X |
| Intake and Output |  |  |  |  |  |  |  | X | X | X | X | X | X | X |  |  |  |  |  |  |  |
| UA + Hypoxanthine |  |  |  |  |  |  |  | X |  | X | X | X | X | X | X |  |  |  |  |  | X |
| PAXgene (RNA) |  |  |  |  |  |  |  | X |  |  |  |  |  | X | X |  |  |  |  |  | X |
| DNA Extraction |  | X |  |  |  |  |  | X |  |  |  |  |  |  |  |  |  |  |  |  |  |
| Inflammatory markers4 |  | X |  | X | X | X | X | X |  | X | X | X | X | X | X |  | X | X | X | X | X |
| Antioxidant markers5 |  |  |  |  |  |  |  | X |  | X | X | X | X | X | X |  |  |  |  |  | X |
| Ox damage markers6 |  |  |  |  |  |  |  | X |  | X | X | X | X | X | X |  |  |  |  |  | X |
| MRI Spectroscopy |  | X |  |  |  |  |  |  |  |  |  |  |  |  | X |  |  |  |  |  |  |
| Blood volume draw | **26.5 ml** | **45 ml** | | | | | | **256.5 ml** | | | | | | | | | | | | | 49 ml |

l

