**2. Objectives**

Primary Objective

The primary outcome is to ascertain whether UA is a pro-inflammatory compound. This aim will be tested both by measuring the concentration of inflammatory markers after short term changes in UA, and by testing the hypothesis that different concentrations of UA modify the inflammatory response induced by a lipid tolerance test.

Secondary Objectives

To document the effect of increasing versus decreasing UA levels on circulating antioxidant biomarkers. To test the hypothesis that increasing levels of UA are associated with higher mitochondrial efficiency as indicated by higher MRI-spectroscopy estimated rate of phosphocreatinine resynthesis after exercise.

Both primary and secondary aims will be tested using two different trials whose results will be complementary. In the first trial (Trial A: UA versus Placebo), the primary and secondary outcomes will be estimated after raising the circulating UA levels by systemic UA infusion.

In the second trial (Trial B: Rasburicase versus Placebo), the primary and secondary outcomes will be estimated after lowering the circulating UA levels by systemic infusion of Rasburicase, a recombinant form of urate oxidase that is already approved for clinical use.

In both Trials, measures will be conducted before and after the intervention and the analysis will be focused on a comparison between active treatment and placebo groups.

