
**Visit 2: history, physical exam and preliminary test**

Participants will arrive at NIA Clinical Research Unit after overnight fasting for 8 hours. A brief physical examination will be performed, including a sample of blood that will be collected for DNA extraction and characterization of the genes that indirectly or directly affect the UA metabolism. A physician will review subject’s eligibility criteria and immediately after the participant will be administered an MRI-spectroscopy that estimates the rate of phosphocreatinine resynthesis after exercise). Next, an Oral Lipid Tolerance Test (OLTT) will be performed. The OLTT consists of eating a standard fast-food type meal (with approximately 900 cal and 50 grams of fat), and measuring changes in lipids and inflammatory markers at 2 hour intervals for total of 8 hours. The meal will be prepared by a registered dietitian and will be consumed in no longer than 20 minutes. The inflammatory markers that will be sampled consist of IL-6, IL-6sr, TNF-α, TNF-r1, TNF-r2, sgp 130, and hsCRP (+Tryglycerides). However, based on the information available at the end of the study, some of these inflammatory markers may not be measured and may be substituted with markers without changing the quantity of blood collected. OLTT will start in the morning after 8 hours of fasting. After the meal, subjects will not eat for the next 8 hours but will have free access to water and ice. After 8 hours a standard meal will be available. Blood samples will be drawn before the meal and every 2 hours after the first bite of the meal over an 8-hour period. The total amount of blood needed for the tests/assays included in the OLTT will be 40 mL including a 1mL waste at each time point. The blood will be sent via courier to NIA Lab at the 2 hour intervals. From there the blood will be sent to the respective labs for processing. After discharge, the patient will be given instruction for the following visit. In particular, participants will be advised to drink 8 8oz glasses of water on the day before the visit and at least 2 further glasses in the morning before the infusion.

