**Visit 3: Baseline and short-term post-intervention**

Visit 3 will be scheduled at least 2 days after Visit 2. Participants will be asked to arrive the evening before Visit 3 for a two consecutive overnight stay at the NIA Clinical ResearchUnit. Below is the sequence of exams and blood tests scheduled for Visit 3. As mentioned above, participants will be requested to drink at least two glasses of water and eat a light breakfast (cold cereal, milk, coffee or tea and bread and butter with butter and/or jelly in the morning). If for some reason, the study participant does not consume an appropriate amount of water on their own 500 mL of normal saline 0.09% will be administered intravenously prior to the study intervention. Based on their characteristics (UA serum level) and sequence of enrollment, participant will be assigned a randomization envelope. After opening the envelope and compiling the included randomization form, the NIA research pharmacist assigns the participant to the treatment or placebo group and prepares the study drug. Information on randomization will be maintained by the NIA research pharmacy in a safe but known place, accessible in case of emergencies. At 4:00 pm following the treatment, participants will eat a dinner consisting of a sandwich and a bag of chips. They may have a soda, coffee, tea or milk. The participant will be not be able to eat again until morning for the lipid tolerance test but will be given water freely.

*1. Basal Metabolic Rate (BMR)*

Basal Metabolic Rate will be estimated in Visit 3 at baseline and on the next day after the intervention. The measurement will be performed in the morning after overnight fasting at the NIA Clinical Research Unit. RMR will be measured before any other evaluation using the COSMED K4 b2 portable indirect calorimeter.

*2. Vital sign measurements*

Blood pressure, pulse rate, respirations and core body temperature will be measured at baseline and at each evaluation time during the following 24 hours. Pulse rate and blood pressure will be estimated using an automated cuff. Core temperature will be estimated using a sublingual thermometer. An EKG will be obtained 24 hours after the beginning of the infusion.

*3. Infusion of the Study Drug*

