Total and differential white and red blood counts, hemoglobin, hematocrit, platelets, glucose, BUN, creatinine, Uric Acid, LDH, CPK, electrolytes, AST, ALT, ALP, albumin, globulin, bilirubin (total and direct), haptoglobin, HDL and total cholesterol, triglycerides, and CRP will be drawn at the 24 hour timepoint to make sure that there has been no change post intervention. The total amount of blood needed for this will be 15 mL.

*11. Urine collection*

A urine sample will be collected at baseline (first morning void on Day 1), every void between 1 and 12 hours after infusion and 24 hours after infusion. The urine samples will be used to evaluate uric acid levels in the urine and potentially markers of oxidative stress damage.

*12. MRI muscle spectroscopy.*

Magnetic resonance spectroscopy (MRS) will be used to study energy metabolism in muscle during and after exercise. As already mentioned, MRS is performed once on Visit 2 and a second time 24 hours after the infusion of the study drug, immediately before performing the second Lipid Tolerance Test. Participants will be carefully screened for MRI contraindications before performing the tests. Also, they will be given a choice of receiving the MRI. Participants with contraindication to MRI or refusing MRI will not receive MRI but will be still enrolled in the other parts of the study, without any effects on their compensation.

*13. Lipid Tolerance Test*

24 hours after the injection, A second OLTT will be performed using exactly the same protocol used in Visit 2.

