Randomization to treatment or placebo: according to the order of enrollment and sex, participants will be randomly assigned to receive treatment or placebo in each cohort.

Data analysis: differences in circulating inflammatory markers and antioxidants, as well as differences in other measurements will be estimated before and after treatment in both cases and controls. In each trial, the time-dependent modification of UA levels will be evaluated and the outcomes will be estimated and compared between cases and controls after intervention.

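### The second lipid test takes a post-randomisation sample as its baseline, and the stated analysis names no covariate role for the pre-randomisation lipid test

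*Protocol*

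**What the plan says.** The primary aim in section 2 of the protocol has two limbs. The second is to be assessed "by testing the hypothesis that different concentrations of UA modify the inflammatory response induced by a lipid tolerance test".

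The test is done twice. At Visit 2 it consists of a standard fatty meal and "measuring changes in lipids and inflammatory markers at 2 hour intervals for total of 8 hours". At Visit 3 the protocol states: "24 hours after the injection, A second OLTT will be performed using exactly the same protocol used in Visit 2".

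The Day 2 column header of the schedule table in section 5 reads "24 h from intervention is the baseline for the second Oral Lipid Tolerance Test". Allocation to treatment or placebo is made at Visit 3, where each "participant will be assigned a randomization envelope" before the infusion. The Visit 2 test therefore precedes randomisation, and the 24 h sample follows both randomisation and infusion.

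On analysis, section 2 says "measures will be conducted before and after the intervention and the analysis will be focused on a comparison between active treatment and placebo groups". The data-analysis paragraph of section 11 asks for differences before and after treatment in both arms, and adds that "the outcomes will be estimated and compared between cases and controls after intervention". Neither place gives a formula for the lipid-test response or a covariate. The only model written out is the random-intercept model for the sample-size simulation. It has time and treatment terms, but no baseline term and no lipid-test term.

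**The concern.** The 24 h draw serves two purposes. It is an outcome sample of the infusion limb and also the pre-meal reference of the second lipid test. If the response is taken as a change from that sample, a quantity that treatment may have shifted is subtracted, and any drift in the shift over the next 8 hours is counted as meal response.

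In Trial A the drift has a predictable direction. If uric acid raises IL-6 and the effect wanes as uric acid clears, the active arm loses part of its excess between 24 and 32 h. The change contrast is then negative and looks as if uric acid blunts the meal response. The rationale for Trial A accepts either an increase or a reduction as a finding, so such a result could be read as real. Uric acid itself is not scheduled for measurement between 24 h and two weeks, so the fall could not be checked afterwards.

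The second issue is precision. With 10 against 10, each person's own untreated lipid test is the obvious covariate. It is already collected, but the analysis text does not put it to that use.

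**Working it through.** The protocol states no power or effect size for the lipid-test limb, so there is no figure of its own to reproduce. Its power figures concern the infusion limb.

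**1. Fade in Trial A under no modification of the meal response**

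Inputs:
- Peak rise in uric acid of 3-4 mg/dL after 500 mg (section 6).
- Elimination half-life of 10.8 h, observed after 1,000 mg (section 14).
- IL-6 coefficients of 0.04-0.08 pg/ml per mg/dL (section 11).
- Assumptions: IL-6 follows uric acid without lag, and decay starts at the end of the 1 h infusion.

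Uric acid excess at time t = peak × 0.5^((t−1)/10.8).

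- At 24 h: 0.5^(23/10.8) = 0.2285 of peak.
- At 26, 28, 30 and 32 h: 0.2010, 0.1768, 0.1555 and 0.1368; mean 0.1675.
- Ratio: 0.1675/0.2285 = 0.733, a fade of −26.7% of the 24 h arm difference.

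| Peak, coefficient | 24 h difference | Mean post-meal difference | Change from 24 h |
|---|---|---|---|
| 3, 0.04 | 0.027 | 0.020 | −0.007 |
| 3, 0.08 | 0.055 | 0.040 | −0.015 |
| 4, 0.04 | 0.037 | 0.027 | −0.010 |
| 4, 0.08 | 0.073 | 0.054 | −0.020 |

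(IL-6, pg/ml.)

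The time course in section 11 gives a similar size. Take a rise of 2.7 mg/dL that falls in a straight line from 2 h to zero at 48 h. At 24 h the excess is 2.7 × 24/46 = 1.409, and its mean over the four post-meal samples is 1.115. The change is −0.294 mg/dL, or −0.012 to −0.023 pg/ml.

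**2. Does it matter against the noise?**

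Section 11 gives an IL-6 SD of 0.02, citing 976 subjects. If 0.02 were a standard error, the SD would be 0.02 × √976 = 0.625. The probabilities below are for the single 24-to-32 h change with 10 per arm, by normal approximation.

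- The fade over that interval is 0.010-0.020 pg/ml on the half-life course (rise 2.7) and 0.019-0.038 on the straight-line course.
- SD 0.02, independent samples: SD of the change = 0.02 × √2 = 0.028. The chance of a spuriously significant result is 0.12 to 0.84.
- SD 0.625, assumed within-person correlation 0.8: SD of the change = 0.625 × √0.4 = 0.395. The chance in the fade direction is about 0.03-0.04, against 0.025 by chance alone.

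**3. Trial B**

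Section 11 postulates that uric acid goes to zero after rasburicase. While it stays there, the arm difference does not drift and there is no fade. If uric acid recovered during the window, the bias would be towards apparent amplification.

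**4. Precision from the Visit 2 test**

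The correlation ρ between a person's two tests is not in the protocol; 0.5-0.8 is assumed. Relative to a post-only comparison, the variance is 2(1−ρ) for a difference from Visit 2 and 1−ρ² for ANCOVA. Power is from the noncentral t, two-sided 5%, 10 per arm, with 18 df (difference) or 17 df (ANCOVA). The true effect is one SD of the outcome, so the standardised effect is 1/√variance.

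| ρ | Variance, difference | Power | Variance, ANCOVA | Power |
|---|---|---|---|---|
| 0.5 | 1.00 | 0.56 | 0.75 | 0.68 |
| 0.7 | 0.60 | 0.78 | 0.51 | 0.84 |
| 0.8 | 0.40 | 0.92 | 0.36 | 0.94 |

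The gains are 0.12, 0.06 and 0.02. Adding sex uses one more degree of freedom and lowers the ANCOVA powers by less than 0.005 before any benefit from sex.

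**The case against.** The strongest reply is that the header is a sampling note. It tells staff that the 24 h draw doubles as the pre-meal draw, and the Visit 2 columns are laid out the same way. No sentence makes change from 24 h the endpoint. A reader might infer that the protocol has decided to judge the response only against that sample and to discard the Visit 2 test. The text does not support this. Sections 2 and 11 ask for before/after comparisons, and Visit 2 is the only lipid test done before treatment. The covariate set may also be in a statistical analysis plan that is not shown. All of this stands, and it limits the point to a misleading label and an analysis text that can be improved.

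A reader might also set ANCOVA against a post-only comparison and claim a power gain from 0.56 to as much as 0.94. That comparator is not the before/after analysis the protocol describes. The fair comparison is the smaller gain shown above.

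Finally, it is tempting to replace the change score with the post-meal level as the single main contrast. With no modification, that level still differs between arms by +0.020 to +0.054 pg/ml, because the infusion effect persists. This is about 2.7 times the fade it removes (0.733/0.267), so the level alone does not answer the question either.

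**Conclusion.** The point holds in a limited form. The protocol calls a post-randomisation sample the baseline of a test that it describes in terms of changes, and its stated analysis assigns no covariate role to the pre-randomisation test.

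In Trial A, a change from 24 h would carry a fade of about −27% of the 24 h arm difference, or −0.007 to −0.020 pg/ml. This rests on no lag between uric acid and IL-6, and on a half-life from a 1,000 mg infusion applied to 500 mg. The fade is material at an IL-6 SD of 0.02 and negligible at about 0.6. The apparent blunting is confined to Trial A and should not be extended to Trial B.

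The precision gain from ANCOVA over a simple difference is 0.02 to 0.12 in power, depending on a correlation the protocol does not give. Adjusting for Visit 2 improves precision but does not remove the fade if the outcome stays a change from 24 h. These are two separate matters, and the fix has to address both.

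**What to change.** In section 11, state that the second lipid-test outcome is compared between arms, within each trial, by ANCOVA adjusting for the same person's corresponding Visit 2 lipid-test value and for sex.

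In the schedule table, call the 24 h value the pre-meal sample of the second test rather than its baseline.

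Report three contrasts together:
- the 24 h level;
- the post-meal level, described as the total effect on post-meal inflammation;
- the change from 24 h.

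State that modification of the meal response will be claimed only from reading the three jointly, since neither the level nor the change isolates it. For example, in Trial A a negative change beside a positive 24 h difference is what fading alone would produce.

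The cost is wording only. Every sample is already scheduled and no visit or assay is added. The price is a less simple conclusion for this limb, because it rests on a joint reading rather than a single test.
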